### Baseline parameters

For all patients enrolled, information on patient characteristics, diagnosis and duration in OPUS treatment will be collected. Data on diagnosis are used as an inclusion criterion while data on duration in OPUS treatment will be used to assess whether the smartphone app has a different effect based on the duration of receiving OPUS treatment. Background characteristics for the clinicians will also be collected. Since preferences in clinical decision making have been found to be related to patient involvement [34], the Clinical Decision Making Style questionnaire (CDMS) will be collected at baseline. The CDMS is a self-reported 21-item measure for the assessment of preferences in clinical decision making [16]. The scale consists of two subscales: 1) Participation in Decision Making (PD) and 2) Information (IN). The questionnaire is rated on a 5-point Likert scale and has been developed in two versions – one for patients and one for provider. The PD subscale has good internal consistency (Cronbach’s α = .85–.89), while the IN subscale has an acceptable internal consistency (Cronbach’s α = .75–.81). The PD and IN subscales do not correlate indicating convergent validity (i.e. preferences for participation in decision making are independent of preferences for information) [16]. In the present study, patients and their primary provider will be asked to complete the questionnaire to determine their level of agreement. The scale will only be used at baseline due to research indicating that the CDMS scoring is moderately to highly stable over 12 months [16].

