### Secondary outcomes

Based on the conceptual framework of Shay and Lafata [18], the study will investigate whether the smartphone app will improve the patient’s preparedness for SDM, self-efficacy, patient’s alliance with the clinician, severity of symptoms, level of functioning, hope, and treatment satisfaction. These outcomes will be obtained at baseline and after 6 months. In addition, the feeling of hope, self-efficacy and communication with one’s clinician will be obtained after 3 months.

The Preparation for Decision Making (PrepDM) scale is a self-reported 10-item instrument to measure the patient’s perception of how useful a decision aid or other decision support intervention is in preparing the respondent to communicate with their practitioner at a consultation focused on making health decisions [36]. The questionnaire is rated on a 5-point Likert scale from “Not at all” (1) to “A great deal” (5) with higher scores indicating a higher level of preparedness to communicate with one’s care provider regarding health decisions. The PrepDM has been validated with high internal consistency (Cronbach’s α = .92 to .96) [36]. The PrepDM scale will be translated to Danish for this study using the forward/backwards translation process. The General Self-Efficacy Scale (GSE) measures the patient’s belief that one’s actions are responsible for successful outcomes [37]. The questions consist of 10 items rated on a 4-point Likert scale ranging from “not at all true” (1) to “exactly true” (4) with higher scores indicating higher self-efficacy. The scale has been validated and found reliable in psychiatric care with the Danish version having good internal consistency (Cronbach’s α = .87) [38].

The Working Alliance Inventory-short (WAI) measures the therapeutic alliance between patients and clinicians within three domains; goals; tasks; and bond [39]. The questionnaire consists of 12 items rated on a 7-point Likert scale, with higher scores indicating better working alliance. The scale has been developed in two versions – one for patients and one for provider – and will in this study be filled out by patients and by the primary providers. Providers will fill out the instrument for each of their own patients participating in the study. The scale has good internal consistency (Cronbach’s α = .83–.98) and high correlation with the original WAI [40].

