### Power and sample size

The power calculation is based on the results of 6 RCT studies investigating patient activation using the Patient Activation Measure as a primary outcome [51–56], and by using the PS Power and Sample Size Calculations program version 3.1.2. This was done due to a lack of RCTs using the CHAI scale. While these studies use a different scale, they do measure the same domain: patient activation. We calculated our planned sample size based on the effect size on patient activation for these 6 studies. These studies had a mean effect size of 0,42, ranging from 0,28 – 0,65. Based on these studies, we expect to find an effect size between our intervention and control group of 0,42. To reach a power 80% and alpha of 0,05 we will need 90 participants in each group to be able to reject the null hypothesis that the population means of the two groups are equal. We plan on having 1 control per intervention subject. With an expectation of approximately 30% dropouts, we will include 130 participants in each group for a total of 260 participants. In addition, we performed sample size calculations for several secondary outcomes. None of these calculations exceeded 260 participants to detect a significant statistical difference for some of our secondary outcomes as well as our primary outcome.

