### Statistical analysis

The analysis will be performed by using the IBM SPSS and SAS. Significance levels below 0,05 will be considered significant for the analysis of primary and secondary outcomes.

The data analysis will be conducted accordingly to the principle of intention-to-treat (i.e. patients will be included in the analysis according to group assignment even if they do not receive all of the planned intervention). In case of missing data, the operation of multiple imputations will be used to address the issue of missing values. To validate the complete case analyses, an analysis of the drop outs will be conducted.

With multiple assessment points, we will use mixed-effects linear regression for the primary analysis. The mixed-effects model is chosen to account for the dependency inherent in the data due to repeated measurements and to allow respondents with missing observations at different time points. If relevant, subsequent statistical tests will be performed. Cohens Kappa will be performed to determine the level of agreement between the patients and providers..

If any of our outcomes do not meet the assumptions for parametric statistical tests, data will either be transformed as appropriate prior to analysis or replaced by non-parametric statistical tests.

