## Discussion

The Momentum trial is to our best knowledge the first randomized controlled trial to evaluate the effectiveness of a smartphone application to engage people with schizophrenia-spectrum disorders in their treatment consultations to support patient activation and SDM. The intervention will focus on supporting patients through the smartphone app to become more active in their care (primary outcome). In addition, the intervention will also connect patients together with their providers (through a web portal) to gain a common starting point before treatment consultations. We expect that the combination of patients becoming more active in their care together with having their data shared with the provider will improve the patient’s preparedness for SDM, the therapeutic alliance, the efficacy of therapeutic interactions, hope, self-efficacy, severity of symptoms and level of functioning (secondary outcomes).

A major strength of the study is the comprehensive pilot study prior to the trial. While the trial is primarily focusing on quantitative assessments, the pilot study was mainly qualitative with a focus on identifying needs and preferences in the target group in relation to a smartphone app to support SDM. Another strength of the study is the focus and assessment on both patient and provider. Research indicates that addressing data from patients and providers together may yield more powerful effects than only focusing on one of the two [8]. Information from both perspectives will also provide valuable information on how patients and providers view their alliance. In addition, providers will be asked to rate the patient’s engagement level to compare this with the patient’s own perceived level of engagement. Finally, we have a solid sample size calculation to perform a data analysis with good strength regarding our primary outcome and several secondary outcomes.

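### Plain Cohen's kappa is named for patient–provider agreement on an ordered Likert instrument (baseline CDMS); a statistic that uses the ordering should replace it

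*Protocol article*

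**What the plan says.** The only sentence on the method is in Statistical analysis: "Cohens Kappa will be performed to determine the level of agreement between the patients and providers". It names no weights, categories, unit of analysis (item or subscale) or alternative.

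Baseline parameters shows what the agreement refers to. For the CDMS, "patients and their primary provider will be asked to complete the questionnaire to determine their level of agreement". On its structure the section says "The CDMS is a self-reported 21-item measure for the assessment of preferences in clinical decision making", and "The questionnaire is rated on a 5-point Likert scale and has been developed in two versions", one for patients and one for providers. There are two subscales, Participation in Decision Making (PD) and Information (IN), each with its own internal consistency. No bands or cut-points are given for either.

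Two other places bring patient and provider ratings together, but neither mentions kappa:

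- Secondary outcomes: the Working Alliance Inventory (WAI) "will in this study be filled out by patients and by the primary providers". It has 12 items on a 7-point scale.
- Discussion: "providers will be asked to rate the patient’s engagement level to compare this with the patient’s own perceived level of engagement".

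**The concern.** Cohen's kappa in its plain form is a statistic for nominal categories: two ratings either match or they do not. CDMS responses are ordered, and its subscale scores are multi-item scores with many possible values. Two difficulties follow.

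- **On subscale scores**, kappa can be of use only after the scores are cut into categories. The article gives no cut-points, and the result depends on how many there are and where they fall.
- **On single items**, the five response options supply the categories, but a patient and provider one step apart count as disagreeing just as much as a pair four steps apart.

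In both cases the coefficient will usually lie well below a measure that uses the ordering. A reader could then take pairs who are mostly close to each other as agreeing poorly. A single kappa also does not show whether providers score systematically higher or lower than their patients, which is part of what a comparison of preferences should reveal.

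**Working it through.** **The plan's own figures.** The article gives no expected agreement, number of categories or precision for this analysis, so there is no figure to reproduce. The trial's sample size rests on the treatment effect ("we expect to find an effect size between our intervention and control group of 0,42") and does not enter here.

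**Inputs.** From the article: plain kappa, 5-point items, two subscales, no categories. Assumed, because the article gives no value: patient and provider scores are bivariate normal with equal variances, and correlation ρ is 0.5, 0.7 or 0.9. With no mean shift, the absolute-agreement intraclass correlation (ICC) of the uncut score equals ρ.

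**Formulas.** Unweighted kappa = (p_o − p_e)/(1 − p_e), where p_o is the observed and p_e the chance proportion of exact matches. Weighted kappa = 1 − Σw·p / Σw·e, where p and e are the observed and chance-expected cell proportions and w = (i − j)² for quadratic weights.

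**One case by hand.** Two categories cut at the median, ρ = 0.5: p_o = 1/2 + arcsin(0.5)/π = 0.667 and p_e = 0.5, so kappa = (0.667 − 0.5)/0.5 = 0.33. Five equal-probability categories, same ρ: p_o = 0.321 and p_e = 5 × 0.2² = 0.20, so kappa = 0.121/0.80 = 0.15. True agreement is identical in the two cases.

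**Number of categories** (equal probability, no mean shift):

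| ICC of uncut score | Unweighted, 2 | Unweighted, 3 | Unweighted, 5 | Quadratic-weighted, 5 |
|---|---|---|---|---|
| 0.50 | 0.33 | 0.24 | 0.15 | 0.45 |
| 0.70 | 0.49 | 0.38 | 0.25 | 0.65 |
| 0.90 | 0.71 | 0.61 | 0.47 | 0.85 |

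**Position of the cut.** With two categories and ρ = 0.5, moving the cut from the median to the 90th percentile lowers kappa from 0.33 to 0.25.

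**Single items.** For a skewed 5-point item (cuts at −2, −1.3, −0.5 and 0.5 SD), unweighted kappa is 0.17 at ρ = 0.5, against 0.44 for both quadratic-weighted kappa and the item ICC. At ρ = 0.7 the figures are 0.29 and 0.63, and at ρ = 0.9 they are 0.54 and 0.83.

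**Systematic shift.** With five categories, unweighted kappa is 0.07 when ρ = 0.3 and the raters differ by 0.5 SD on average. It is also 0.07 when ρ = 0.9 and they differ by 1 SD. The ICCs are 0.27 and 0.60. One kappa value therefore covers two very different situations. Unweighted kappa was below the ICC in every scenario run: ρ from 0.3 to 0.9, with shifts of 0, 0.5 and 1 SD.

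**The case against.** The strongest reply is that the article does not say unweighted, and does not say that subscale scores will be cut. A condensed article may leave weights and the unit of analysis to an analysis plan that is not shown. Item by item, the categories are the response options and are not arbitrary. With quadratic weights, most of the gap disappears (0.65 against 0.70 in the middle row of the table). Kappa and the ICC are also different quantities, so a lower kappa is not in itself a biased ICC.

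Much of this stands. A reader might infer that the result must rest on arbitrary categories and must understate agreement. The text does not support that as a certainty: it holds only for kappa as named, and the arbitrary cuts arise only for subscale scores. What remains is that the article commits to a named statistic, that the name without qualification ordinarily means the unweighted form, and that this form ignores ordering on items and subscales alike. The fallback in Statistical analysis to transformation or non-parametric tests concerns the assumptions of parametric tests and does not cover this.

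A reader might also infer that kappa is planned for the WAI, or for provider-rated engagement against the patient's own view. No sentence says so. Only the CDMS is expressly collected to determine agreement, and the Discussion speaks merely of comparing engagement ratings. Nor does the article make CDMS agreement a main strength of the trial. The Discussion lists assessment of both parties as one further strength, and the examples it gives are alliance and engagement.

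Finally, no single coefficient displays a systematic shift, and that includes the ICC. The mean difference has to be reported beside it.

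**Conclusion.** The point holds in a limited form. The article fixes a nominal-category statistic for agreement on an ordered instrument and defines no categories. For assumed correlations of 0.5 to 0.9 and five equal-probability categories, unweighted kappa would be about 0.15 to 0.47, where quadratic-weighted kappa would be about 0.45 to 0.85. These sizes rest on assumed normality, equal variances, no mean shift and a correlation that the article does not give. The direction was the same in every scenario examined, but the amount for this trial is unknown.

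The importance is minor. The CDMS is collected only at baseline, and agreement is not among the stated hypotheses. A reader might infer a threat to the trial's main result, but no treatment effect, primary outcome or sample size depends on this analysis.

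**What to change.** For the CDMS PD and IN subscale scores, replace kappa with:

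- an absolute-agreement ICC with a confidence interval;
- the mean patient–provider difference and limits of agreement;
- intervals that allow for several patients sharing one provider.

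If single items are compared, name quadratic-weighted kappa. If agreement on the paired WAI scores is also analysed, treat them like the CDMS subscales; otherwise nothing needs to change there.

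The cost is a change of wording in the analysis plan and slightly more analysis work, with standard procedures in the packages already named (SPSS and SAS). No new data are needed.

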### Primary outcome

The primary outcome of this trial is the difference in patient activation before participating in the trial and after 6 months participation. This will be assessed using the Consumer Health Activation Index for mental health (CHAI-MH) [35]. The 10-item instrument was developed based on 5 key domains: knowledge, self-efficacy, motivation and beliefs, actions, and internal locus of control. The questionnaire is rated on a 6-point Likert scale ranging from “Strongly disagree” to “Strongly agree”. Afterwards, the scores are transformed into a theoretical value from 0 to 100, with higher scores signifying a stronger involvement in the treatment and confidence in the ability to take care of one’s own health and health treatment. Higher CHAI scores have been associated with fewer depressive and anxiety symptoms. CHAI has been found valid and reliable while having good internal consistency (Cronbach’s α = .91) [35]. For this study the CHAI was modified to mental health. Hence, the mental health version of CHAI (CHAI-MH) has not yet been validated. The CHAI-MH was translated to Danish using a thorough forward/backwards translation process with three independent translators.

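### The fallback to a transformation or a non-parametric test covers the primary outcome, so the primary analysis and its effect measure can change with the observed data

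*Protocol article*

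**What the plan says.** All the analysis wording is in the Statistical analysis section of the protocol article. It states that "we will use mixed-effects linear regression for the primary analysis" and gives the reasons for that model: "to account for the dependency inherent in the data due to repeated measurements and to allow respondents with missing observations at different time points". The section closes with a general fallback. Its condition is "If any of our outcomes do not meet the assumptions for parametric statistical tests" and its action is that "data will either be transformed as appropriate prior to analysis or replaced by non-parametric statistical tests".

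Three other statements bear on this:

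- Primary outcome defines the endpoint as "the difference in patient activation before participating in the trial and after 6 months participation".
- Primary outcome also says of the CHAI-MH items that "the scores are transformed into a theoretical value from 0 to 100", and that "the mental health version of CHAI (CHAI-MH) has not yet been validated".
- Power and sample size sets the target as being able to "reject the null hypothesis that the population means of the two groups are equal".

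The Statistical analysis section also plans multiple imputation for missing values under intention-to-treat, and does not tie it to one model.

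**The concern.** The condition applies to every outcome, and CHAI-MH is not carved out. The article offers two actions and no rule for choosing between them. Nor does it say that the choice is made blind to allocation. As written, the primary analysis is settled only after the primary data have been examined.

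For the primary outcome this has two consequences. First, what is estimated can change: the effect may be reported in CHAI-MH points, on a transformed scale, or as a rank comparison. Second, the non-parametric route sets aside the two properties for which the article chose its model, namely the handling of repeated measurements and the use of patients with incomplete follow-up. With about 30% dropout expected, the second property matters. At stake are the interpretability of the main result and its defence against the charge that the test was picked after the fact.

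**Working it through.** **1. The plan's own figure.** Inputs from Power and sample size: effect size 0.42, power 80%, alpha 0.05, 1:1 allocation, 30% dropout. Two-sided testing is assumed, as sidedness is not stated.

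- Normal approximation: n = 2(1.960 + 0.842)² / 0.42² = 15.70 / 0.1764 = 89.0 per arm. The exact two-sample t-test gives 89.96, so 90, as stated. A one-sided test would give 71 and does not match.
- Dropout: 90 / 0.70 = 128.6, so 129, against 130 stated.
- Completers: 130 × 0.70 = 91 per arm.

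The sample size reproduces as a comparison of two means. This point does not affect it.

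**2. What each route does to the primary analysis.**

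| Route | Mixed model kept? | Effect measure | Hypothesis powered? |
|---|---|---|---|
| Planned model | Yes | CHAI-MH points | Yes, difference in means |
| Transformation | Can be kept | Transformed scale | Means of the transformed score |
| Standard two-group rank test | No | Rank comparison | No |

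**3. Type I error.** The documents give no distribution for CHAI-MH, so these inputs are assumptions: 91 per arm, no true effect, one score per patient, simple two-group tests, 10,000 replicates, and a Shapiro-Wilk check at 0.05 as the gate. Two score distributions were used: a normal one (mean 65, SD 15, clipped to 0-100) and a left-skewed one (100 × beta(4, 1.5)). The transformation was log(101 − score). Monte Carlo standard error near 5% is √(0.05 × 0.95 / 10,000) = 0.2 points.

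| Behaviour | Normal | Skewed |
|---|---|---|
| t-test always | 4.7% | 5.3% |
| Fixed gate: t-test, else Mann-Whitney | 4.8% | 5.4% |
| Gate fails, then smaller p of log-t and Mann-Whitney | 4.9% | 6.6% |
| Free choice among all three | 7.4% | 7.6% |

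The gate failed in 4.9% of normal samples and 99.99% of skewed ones. A separate run gave 5.0% for the fixed gate, 6.3% for the open choice after a failed gate, and 7.7% for free choice.

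**4. Power cost of ranking, like for like.** On normal data the rank test has relative efficiency 3/π = 0.955, so 91 per arm acts like 91 × 0.955 = 86.9.

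- Means: 0.42 × √(91/2) − 1.960 = 0.873, power 0.81.
- Ranks: 0.42 × √(86.9/2) − 1.960 = 0.809, power 0.79.

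A simulation (6,000 replicates, 91 per arm, assumed baseline-to-follow-up correlation 0.5) agrees:

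- 6-month scores: 0.783 (ranks) against 0.804 (means).
- Change scores: 0.792 against 0.808.
- With baseline adjustment: 0.879 against 0.900.

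The loss is about 2 points each time.

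**The case against.** The strongest reply is that this is one generic sentence, conditional on failed assumptions, and that the diagnostic, threshold and named tests belong in a statistical analysis plan that is not shown. That is right about the missing detail, and none of it is counted here. It does not answer the point, because the article itself permits the primary analysis to be replaced. A later threshold would carry out that switch, not remove it.

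It can also be said that the switch may never operate for CHAI-MH. The Assessments section reports no ceiling effects in a pilot of 21 patients. This is the document's only evidence on the distribution, and it lowers the likelihood of a switch. But 21 patients cannot settle the shape of the residuals in the trial, and the scale is bounded and, in this version, not validated.

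Four stronger readings are tempting, and the documents do not support them:

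- **That any check-then-switch rule inflates type I error.** A fixed gate stayed near 5%. Inflation needs the analyst to favour the smaller p-value, which the text leaves open but does not state.
- **That the fallback costs about ten points of power.** A reader could set an unadjusted rank test (about 78%) against a baseline-adjusted model (about 90%). Almost all of that gap is baseline adjustment, which the article does not state, and the 90% rests on an assumed correlation of 0.5.
- **That missing data would be unhandled under the fallback.** The same section plans multiple imputation, which can precede a transformed or rank analysis. What a standard rank test loses is the mixed model's own use of incomplete patients.
- **That the fallback always drops the model.** A transformation can keep it and change only the scale.

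**Conclusion.** The point holds in a limited form. The fallback reaches the primary outcome, offers two routes with no rule between them, and so lets the observed data determine both the primary test and the quantity it estimates. On the non-parametric route it also runs against the article's own reasons for the mixed model and its own powered hypothesis.

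The numerical damage is small: none to speak of under a fixed gate, about 1.3-1.6 points above 5% if the smaller p-value is taken after a failed check, and 2-3 points in the worst case of free choice. These figures rest on assumed score distributions and simple two-group tests, not on the mixed model itself. Under the same assumptions the untransformed comparison of means held close to 5% on the skewed score, so the switch buys no needed protection. The change of effect measure is the more important cost. This is a cheap improvement, not a demonstrated threat to the result.

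**What to change.** Exempt the primary outcome from the fallback sentence. State that the mixed-effects model on the untransformed CHAI-MH score is the primary analysis whatever the residual diagnostics show, with robust (sandwich) or bootstrap standard errors. Report transformed or rank-based analyses of CHAI-MH only as sensitivity analyses, labelled as such. The choice of models for the secondary outcomes can stay with the statistical analysis plan.

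The cost is a change of wording, slightly more analysis work, and a small possible loss of efficiency if the score proves very skewed. Sample size and trial conduct do not change.
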